### Statistical analysis plan

Primary analysis will compare randomised clusters using an intention to treat approach. Characteristics of clusters will be summarized at baseline and across study arms (SHQIP or usual practice).

Analyses of the primary endpoint will be based on generalized linear mixed models to account for within and between cluster variability. The generalized estimating equation approach, with robust standard errors, will be adopted, using STATA 12.0 (College Station, TX, USA) statistical analysis software. Initial analyses will be simple, unadjusted comparisons of randomised clusters. If there appear to be any important imbalances between randomised groups in terms of baseline covariates, adjusted analyses will also be performed. All effects will be estimated with a 95% confidence intervals and p-values from the corresponding hypothesis tests. Statistical significance will be taken as two sided p-value less than 0.05, with no adjustment for multiple comparisons.

There will be two main analyses. First, after one year of follow-up there will be a comparison between the first and second round communities, assessing the effect of the intervention after one year. Second, after two years follow-up there will be a comparison between the first round and third round clusters, assessing the effect of the intervention after two years. The investigators recognize that a range of sexual health program activities will be taking place across communities throughout the duration of STRIVE. Systematic monitoring of these activities as described in Table 2 will allow us to compare them, both qualitatively and quantitatively, between SHQIP and usual practice communities.

There are a few envisaged limitations to the STRIVE protocol. Firstly the STRIVE study will determine if implementing a CQI approach is effective in reducing STI rates, but will not address the issue of testing for STIs among community members who do not attend a health service. At this point we do not know what proportion of the community do not attend a health service, especially in the younger age groups within the 16–34 year age bracket.

Secondly the STRIVE study is powered to detect a 50% decline in STI prevalence but it is possible that reductions may be less than this. However, a 50% reduction in prevalence would still leave rates at between 4 and 30 times higher, and the level of STI care provided after the SHQIP program will still be comparable to what is provided in health services accessible to Australians not living in remote communities.

Other key challenges to STRIVE are those characteristic of remote environments and include the need to sustain the motivation of clinic staff to participate in STRIVE while addressing the multiple competing health priorities, as well as high staff turnover.

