### Randomisation

Towards the end of the preparatory period, eight trial clusters (designated “first year trial clusters”) were randomly selected to receive the SHQIP in the second year. Towards the end of the second year of STRIVE, a further eight trial clusters were randomly allocated to the SHQIP in the third year and fourth years.

Randomisation occurs after participation agreements have been signed and the baseline STI prevalence survey has been conducted. Trial clusters are randomised to the SHQIP or usual care using a minimisation approach that aims to balance population testing coverage rates, cluster population size and geographic region across the baseline levels in each trial cluster. The statistician, who was blinded to the study sites (regions), prepared the randomisation list for each geographical area. The protocol was implemented in four regions of Australia in mid 2010.

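### GEE with robust standard errors on 8 v 8 clusters, with no small-sample correction or t reference stated, does not assure the nominal 5% level

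*Protocol article*

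**What the plan says.** All references are to the protocol article.

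- **Model.** The Statistical analysis plan section first says: "Analyses of the primary endpoint will be based on generalized linear mixed models to account for within and between cluster variability". The next sentence reads: "The generalized estimating equation approach, with robust standard errors, will be adopted", and names Stata 12.0 as the software. No link function, sandwich variant or reference distribution is given.
- **Level.** "Statistical significance will be taken as two sided p-value less than 0.05, with no adjustment for multiple comparisons".
- **Adjustment.** The initial analyses are unadjusted. Adjusted analyses are added only if important baseline imbalance appears.
- **Main comparisons.** In the first, "after one year of follow-up there will be a comparison between the first and second round communities"; in the second, "after two years follow-up there will be a comparison between the first round and third round clusters".
- **Clusters per round.** The Study design section gives 24 clusters, one third entering the programme at each step. Under Randomisation, "eight trial clusters (designated “first year trial clusters”) were randomly selected to receive the SHQIP", and later "a further eight trial clusters were randomly allocated to the SHQIP". That leaves 24 − 16 = 8 for the third round.
- **Allocation.** The Randomisation section uses minimisation on testing coverage, cluster population size and geographic region.

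**The concern.** The sandwich variance is justified when the number of clusters is large. Here each main analysis has 16. The 68 communities do not help, because the cluster is the randomised unit. With few clusters the uncorrected sandwich is too small on average, and a normal reference ignores the uncertainty in estimating it. Both make confidence intervals too narrow and p-values too small. The analysis concerns a primary outcome, STI prevalence, and is done twice without multiplicity adjustment.

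A lesser issue is that two model families are named for the same analysis. A mixed model and GEE can target different effects and have different standard errors, and the text should name one.

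**Working it through.** **Inputs**
- Clusters per arm c = 8, so 2c − 2 = 14 degrees of freedom (Study design; Randomisation; Statistical analysis plan).
- Prevalence 15% and an average of 65 people per cluster (Sample size), or 50 men + 50 women = 100 (Prevalence assessment).
- Between-cluster CV: 0.42 as stated, or 8.45/15 = 0.563 from the stated SD (Sample size). Both were tried.
- Assumed, because the article does not say: logit link, uncorrected sandwich, normal reference.

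The only error rate that the article gives is the nominal 0.05. Its figure of 14 clusters needed is a separate matter and is not used here.

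**Step 1: analytic rate, allocation unrelated to outcome.** With equal cluster sizes the uncorrected sandwich variance averages (c − 1)/c = 7/8 of the unbiased one.
- Uncorrected, z reference: P(|t14| > 1.96 × √(7/8)) = P(|t14| > 1.833) = 8.8%.
- With N/(N-1) = 16/15: P(|t14| > 1.96 × √(7/8 × 16/15)) = P(|t14| > 1.894) = 7.9%.
- Unbiased variance, z reference: P(|t14| > 1.96) = 7.0%. The choice of z alone therefore takes the rate above 5%.
- Interval width: 2.145/1.833 = 1.17, so a 95% interval based on t14 and an unbiased variance is about 17% wider.

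**Step 2: simulation under no effect** (beta-binomial clusters, 40,000 trials per setting, 65 or 100 people, CV 0.42 or 0.563)

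| Test | Null rejection |
|---|---|
| Uncorrected sandwich, z | 8.9–9.6% |
| With N/(N-1), z | 7.9–8.7% |
| Sandwich scaled for degrees of freedom, t14 | 5.0–5.6% |
| Cluster-level t-test | 4.7–5.1% |

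A standard exchangeable GEE routine gave 8.4% and 10.2% uncorrected (1,500 trials each, so a standard error of about 0.7 points). Its bias-reduced sandwich gave 5.5–5.8% with z and 3.5–3.7% with t14 (600 trials each), so that combination may be slightly conservative.

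**Step 3: allow for the minimisation.** As an idealisation, arms are perfectly balanced in pairs on a factor that explains a share of the between-cluster variance, and the analysis ignores that factor (CV 0.42, 65 or 100 people).

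| Share explained | Uncorrected, z | Scaled sandwich, t14 |
|---|---|---|
| 0% | about 9.2% | about 5.3% |
| 10% | 8.0–8.4% | 4.4–4.6% |
| 30% | 5.9–6.6% | 3.1–3.4% |
| 50% | 4.1–4.6% | 1.9–2.3% |

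Balancing makes an unadjusted test conservative, which offsets the sandwich bias by an amount that the article does not let one determine. The last column shows that a small-sample correction alone, without adjustment, can go too far the other way.

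**Step 4: size of the model conflict.** For 15% v 7.5% the population-averaged odds ratio is (0.075/0.925)/(0.15/0.85) = 0.459. The cluster-specific odds ratio is about 0.451 at CV 0.42 and 0.443 at CV 0.563, a difference of about 2% to 5% in the log odds ratio.

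**The case against.** The strongest reply has three parts.

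*The text does not say that the standard errors are uncorrected.* This is so. It says only that they are robust, and a fuller analysis plan could specify a correction and degrees of freedom. A reader might infer that the plan rules these out, but it does not. What stands is that the article fixes the method, the level and the 16-cluster comparisons, and its wording taken as written leads to the default sandwich.

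*The simulated 8–10% ignores the minimisation.* This also stands. A reader might infer that the true type I error is 8–10%, about double the nominal level. The document supports that only if the balancing factors are weakly prognostic. Step 3 gives a range from about 4% to about 9%, and nothing in the article places the trial within it.

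*The two model names are loose wording.* Largely accepted. GEE is the method said to be adopted. No link is named, and with an identity or log link and a random intercept the two effects coincide. On the logit scale the gap is small (step 4). A reader might infer incompatible analyses with materially different answers, but the figures do not show that. It remains a wording conflict to resolve.

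**Conclusion.** The point holds in conditional form. With the usual sandwich variance and a normal reference, each 8 v 8 comparison would reject about 9% of null trials at the nominal 5% (about 8% with the N/(N-1) factor) if the minimisation factors are weakly prognostic. The rate would be about 6% or 4% if those factors explain 30% or 50% of between-cluster variance. The stated analysis therefore does not assure its stated level, and its actual level cannot be worked out from the document.

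This rests on a logit link, on the uncorrected variance and normal reference being the ones used, and on an idealised model of the balancing. The result is not sensitive to 65 or 100 people per cluster or to which CV is taken. The calculations cover the prevalence outcome only, not the best-practice indicators.

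**What to change.** Rewrite the analysis paragraph to do the following:

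1. Name GEE as the one primary model, state its link, and delete the mixed-model sentence.
2. Use a small-sample-corrected sandwich (Mancl–DeRouen or Kauermann–Carroll) with a t reference, df = clusters minus cluster-level parameters. Alternatively, use a cluster-level t-test or regression on cluster prevalences.
3. Adjust in the primary analysis for the minimisation factors (baseline testing coverage, cluster size, region), keeping the terms few. Alternatively, use a randomisation test that reproduces the minimisation.

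No data collection changes. Intervals widen and apparent power falls. In simulation at 15% v 7.5%, CV 0.42 and 65 people per cluster, power goes from about 75% uncorrected to 61–64% for the scaled sandwich with t14 or the cluster-level t-test, before any gain or loss from adjustment. Part of the higher figure comes from the inflated error rate. Adjustment also spends degrees of freedom: linear terms for coverage and size plus a four-level region factor would leave 16 − 2 − 5 = 9, which raises the critical value from 2.14 to 2.26. That is why the terms should be few, or the randomisation test preferred.

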## Background

For almost two decades sexually transmissible infection (STI) diagnoses have occurred at hyperendemic rates in many remote Australian Aboriginal and Torres Strait Islander (hereafter referred to as ‘Aboriginal’) communities [1]. Data on prevalent and incident infection in these settings are derived from routine notifications reportable by public health agencies and sporadic prevalence surveys conducted in the context of screening programs [2].

In 2011 the diagnosis rates of *Chlamydia trachomatis* (chlamydia) and *Neisseria gonorrhoeae* (gonorrhoea) among Aboriginal people resident in remote communities were 8 and 61 times greater than in the non-Indigenous population [1]. A similar situation exists for *Trichomonas vaginalis* (trichomonas) in the Northern Territory, the only jurisdiction which requires notification of this infection [3]. The majority of these three STIs are notified among people aged 15–29 years [1].

While differential patterns of testing may play some role in these discrepant rates of diagnosis, a major component of the disparity [1] is almost certainly attributable to inadequate access to early detection and appropriate treatment programs offered in primary health care settings [4].

Chlamydia, gonorrhoea, and trichomonas are fully curable STIs but are often asymptomatic for long periods and can lead to serious complications if untreated [5]. For example, untreated chlamydia infection may potentially cause pelvic inflammatory disease (PID), ectopic pregnancy and tubal factor infertility among women [6,7]. In the Top End of the Northern Territory, 26% of all Aboriginal women were found to have had history of PID [8]. Chlamydia can also result in adverse pregnancy outcomes including premature labour and birth, low birth weight, intrauterine growth restrictions, postpartum endometritis [9,10] and a range of neonatal infections including infectious conjunctivitis and pneumonitis [5]. Gonorrhoea has similar sequelae to chlamydia and can also lead to disseminated infection [5]. Trichomoniasis among women is associated with premature rupture of membranes, premature delivery and low birth weight [11,12] while trichomoniasis in men is an important cause of non gonococcal urethritis and is associated with prostatitis [13,14]. All three STIs are associated with an increased risk of HIV transmission [15,16].

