### Data collection methods and variables

The trial uses a number of methods to collect data (Table 2).

**Table 2 T2:** Tools, methods and description of information collected in the trial

**Tool**	**Method and frequency**	**Description of data collected**
Site description assessment	• Conducted by regional STRIVE Coordinators at baseline and the start of each year in all health services	*Broad description of:*
	• Updated annually with any contextual information that may impact on delivery of STI services	(i) Current sexual health activities, including health promotion activities
Systems Assessment	• Conducted by regional STRIVE Coordinators annually in health services randomised to the SHQIP	*Information on:*
		(i) Health hardware
		(ii) Clinical services
		(iii) Patient information systems
		(iv) Health promotion
		(v) Organizational commitment to sexual health
		(vi) Surveillance and evaluation
Quantitative STI testing and clinical management data	• Collated from one or more of the following sources:	(i) Patient consultation data and associated demographics
	(i) Health service patient information management systems	(ii) STI testing, retesting and treatment outcomes Laboratory test result
	(ii ) STI templates within patient management systems	
	(iii) Contact tracing forms	
	(iv) Laboratory data	
	• Extracted 6 monthly for all health services	
STI prevalence assessment	• Each person attending the clinic aged 16-34 will be offered a STI screening test for all three STIs	(i) Prevalence of chlamydia, gonorrhoea and trichomonas in 16-34 year olds in STRIVE trial clusters
	• 50 men and 50 women from each cluster will be included	
	• Takes place on an annual basis in all health services	

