### Prevalence assessment

At the start of each year and prior to initial randomisation the prevalence of chlamydia gonorrhoea and trichomonas will be assessed in clients attending participating health services. The assessment will involve screening 50 male and 50 female resident clients aged 16–34 years per cluster. All those in the age group attending the health service in the prevalence assessment period will be offered testing, unless they have had a test within the preceding three months. For clusters with more than one primary health care centre, the target numbers of 50 men and women will be allocated proportionately according to the number of health services and the size of the community served. The prevalence will be assessed again at the end of the study (Figure 1).

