### Sample size

Power calculations were performed using the method of Hayes and Bennet [34] for cluster randomised trials. Estimates of between and within cluster variability in the primary end point were based on prevalence of the selected STIs in 2006 (the most recent prevalence data available) among Aboriginal people aged 14–34 years in central Australia [35]. Prevalence of chlamydia and gonorrhoea was estimated to be 15%, with an average 65 people tested in each cluster for chlamydia and gonorrhoea. Based on the 2006 notification data, between community variability was estimated as corresponding to a standard deviation of 8.45%, and the within community co-efficient of variation of 0.42. A total of 14 clusters are needed to detect a reduction in chlamydia and gonorrhea prevalence from 15% in control clusters to 7.5% in SHQIP clusters with 80% power and allowing for differing average numbers of people screened in each cluster (2-alpha = 0.05, with no adjustments for multiple comparisons), and equal numbers of clusters in each arm.

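### Follow-up prevalence surveys are fresh samples with no age control, and the plan's only trigger for adjustment looks at baseline, so it cannot respond to their age mix

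*Protocol article*

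**What the plan says.** **Who is surveyed.** The Prevalence assessment section sets up repeated cross-sections, not a cohort: "At the start of each year and prior to initial randomisation the prevalence of chlamydia gonorrhoea and trichomonas will be assessed in clients attending participating" (the sentence ends with the services taking part). The numbers are fixed by sex: "The assessment will involve screening 50 male and 50 female resident clients aged 16–34 years per cluster". Table 2 repeats this: "50 men and 50 women from each cluster will be included". No quota or stratum is set for age within 16–34. People tested in the previous three months are not offered the survey test.

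**Randomisation.** The Randomisation section names testing coverage, cluster population size and region as the minimisation factors. Age structure is not among them.

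**Analysis.** The Statistical analysis plan section starts from a crude contrast: "Initial analyses will be simple, unadjusted comparisons of randomised clusters". Its only provision for adjustment depends on what the baseline comparison shows: "imbalances between randomised groups in terms of baseline covariates, adjusted analyses will also be performed".

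**Reporting.** The Outcome measures section calls for all outcomes to be tabulated by gender and by four age bands (16–19, 20–24, 25–29, 30–34), among other factors. It does not say that the effect of SHQIP is adjusted for these bands or standardised to them.

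**The concern.** The effect is estimated from people surveyed after the program has started. They are whoever attends that year, so their age mix is a feature of the follow-up sample and not a baseline covariate. A rule that looks at baseline imbalance may add adjustment for something harmless and stay silent about a real age difference in the year-one or year-two samples.

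Two different things are at stake:

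- **Precision.** If prevalence varies with age, differences in age mix between clusters add avoidable noise to a comparison of eight clusters with eight.
- **Possible bias.** Randomisation balances the age structure of communities on average. It does not protect the mix of people who attend and are eligible once SHQIP is running, and two features could change that mix. Services in SHQIP receive a one-off $2,000 payment for promotion meant to bring young people in for testing. SHQIP also pushes annual testing and retesting at two to four months, so the three-month exclusion may remove different people in the two arms.

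If infection is commoner in the young, the first route would tend to hide a benefit and the second could exaggerate one. The net direction cannot be known beforehand.

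**Working it through.** **1. Can the stated trigger detect the problem?** Set the sections side by side. The survey is redrawn each year from attenders, and the trigger is an apparent imbalance in baseline covariates. The age mix of a later survey is not observed until that survey is done. The trigger therefore cannot respond to it, whatever the baseline table shows.

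**2. How large could the effect be?** The protocol gives no figure for prevalence by age, so there is no stated result to reproduce. The plan figures used are the 15% control prevalence and the target effect from the Sample size section, 15 − 7.5 = 7.5 points. The rest is assumption: an equal split over the four age bands, and three gradients that each average 15%.

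Move a share *s* of one arm's sample from the two younger bands to the two older ones, split evenly. Crude prevalence then changes by

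shift = *s* × (mean prevalence under 25 − mean prevalence 25–34).

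| Assumed prevalence by band, youngest to oldest (%) | Under 25 | 25–34 | Gap | s = 5 points | s = 10 points | s = 20 points |
|---|---|---|---|---|---|---|
| 18 / 16 / 14 / 12 | 17.0 | 13.0 | 4.0 | 0.2 | 0.4 | 0.8 |
| 22 / 17 / 12 / 9 | 19.5 | 10.5 | 9.0 | 0.45 | 0.9 | 1.8 |
| 28 / 17 / 9 / 6 | 22.5 | 7.5 | 15.0 | 0.75 | 1.5 | 3.0 |

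At *s* = 10 points, as a share of the target effect: 0.4/7.5 = 5%, 0.9/7.5 = 12%, 1.5/7.5 = 20%.

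**3. How large a gap could chance produce?** Take half the sample as under 25. Eight clusters give 8 × 100 = 800 people per arm at full quota, or 8 × 65 = 520 at the number used in the Sample size section.

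- Simple sampling: SE of the difference in the under-25 share = √(2 × 0.5 × 0.5/800) = 2.5 points, or √(2 × 0.5 × 0.5/520) = 3.1 points.
- With an assumed design effect of 4, these double to 5.0 and 6.2 points.

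A 10-point gap is then about 10/6.2 = 1.6 to 10/5.0 = 2.0 standard errors. A 20-point gap is 3.2 to 4.0 standard errors, so by chance alone it is remote.

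**4. Sex.** With the 50/50 quota met in both arms, sex mix contributes 0 points. If one arm reached 55/45, the shift would be 0.05 × (18 − 12) = 0.3 points, or 0.05 × (20 − 10) = 0.5 points, under assumed prevalences by sex.

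**The case against.** The strongest reply is that clusters are randomised. Variation in age mix between clusters is already part of the between-cluster variability that the mixed-model/GEE analysis with robust errors is there to absorb. An unadjusted comparison is then valid, and preferring an adjusted one is a choice of method, not the correction of an error. The unadjusted analyses are called initial, the age-band tabulations would make a difference visible, and a fuller analysis plan may say more.

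Much of this stands. Chance differences do not bias the estimate, and the interval allows for them. It does not answer two points. Tabulating by age band is reporting, not adjustment of the effect. And the article does not leave adjustment open: it fixes a rule, conditional on baseline, that looks in the wrong place.

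A reader might also infer more than the documents support:

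- **That sex mix is equally uncontrolled.** The quota fixes it unless quotas are missed, and missed differently by arm. The power paragraph's phrase "with an average 65 people tested in each cluster" is a planning assumption. It forecasts no shortfall against 100 and says nothing about sex.
- **That the Background section proves an age gradient.** It says: "The majority of these three STIs are notified among people aged 15–29 years". Ages 16–29 are 14 of the 19 single years in 16–34 (74%), so within the trial's age range a majority there would be expected even with flat prevalence. Notifications also depend on who is tested.
- **That some 40% of the target effect is at risk.** That needs the steepest assumed gradient and a 20-point gap, which chance would hardly produce.
- **That bias is established.** It is not. It requires SHQIP to change who is surveyed, which the design makes plausible but nothing here shows.

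**Conclusion.** The point holds for age, at modest size. The stated rule cannot respond to the age mix of the follow-up samples, and age is controlled neither by quota nor by minimisation. A 10-point difference in age mix would move the crude contrast by about 0.4 to 1.5 points, or 5 to 20% of the 7.5-point target. This rests on assumed age gradients, an equal four-band split and an overall prevalence of 15%. With flat prevalence by age the effect would be nil.

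The sure cost is some precision; bias is conditional on SHQIP altering attendance or eligibility by age. This does not invalidate the unadjusted comparison. It is a worthwhile and inexpensive improvement on a judgement-based trigger.

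**What to change.** In the Statistical analysis plan section, for the prevalence outcome, replace the baseline-imbalance trigger with prespecified adjustment. Fit the model to individual survey records at every survey with the four age bands from the Outcome measures section as covariates and sex as a design stratum, whatever the baseline table shows. Keep the crude comparison as a supporting result.

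If standardised arm prevalences are reported, use one fixed age-sex distribution that the trial can obtain. Examples are the pooled survey sample, or the clinic population (residents who attended in the preceding two years) described under Indicator reports. A distribution for all residents may not be available, since the protocol says the proportion who do not attend is unknown.

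The outcomes are already to be broken down by age band and gender, so no new data collection is needed. The costs are:

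- four more parameters (three for age, one for sex) with only 16 clusters per comparison, so the model should stay small;
- under a logit link, an odds ratio conditional on age and sex and not a marginal one, unless marginal standardised effects are reported;
- no protection against other forms of selection among attenders, which age adjustment does not remove.

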## Methods

### Study design

STRIVE is a community-based stepped-wedge cluster randomised controlled trial. During the first 18 months of the trial, 24 ‘trial clusters’ comprising 68 remote communities and primary care centres in Central and Northern Australia were recruited to participate in the trial, and undergo preparatory procedures. The trial clusters are the unit of randomization and comprise either a single community or several communities that share close cultural affinities and/or are geographically proximal. The clusters were determined by the research team in consultation with stakeholders and are located in remote Australia, in the Northern Territory (18 clusters), Western Australia (3 clusters) and Queensland (3 clusters).

At the start of each of the three years, one third of the clusters are randomly assigned to receive the SHQIP (see Figure 1). Clusters not randomised to receive the SHQIP continue to undertake usual STI care. By the start of year four, all clusters will be receiving the SHQIP.

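### The one-year main analysis leaves out eight randomised clusters that are still on usual care and surveyed at the same time; 8 v 16 would raise power from about 60% to 82% on the plan's own inputs

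*Protocol article*

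**What the plan says.** Study design (protocol article) enrols 24 clusters and starts the SHQIP in one third of them, that is eight, at each of three yearly steps. For the rest, "Clusters not randomised to receive the SHQIP continue to undertake usual STI care". Of the prevalence survey, Table 2 says: "Takes place on an annual basis in all health services". The Prevalence assessment section sets 50 men and 50 women per cluster and adds a survey at the end of the study.

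The Statistical analysis plan section names two main analyses: "First, after one year of follow-up there will be a comparison between the first and second round communities", and "Second, after two years follow-up there will be a comparison between the first round and third round clusters".

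The Sample size section uses the Hayes and Bennett method and concludes: "A total of 14 clusters are needed to detect a reduction in chlamydia and gonorrhea prevalence". The effect and power behind that number are a fall "from 15% in control clusters to 7.5% in SHQIP clusters with 80% power". The calculation is two-sided ("2-alpha = 0.05, with no adjustments for multiple comparisons), and equal numbers of clusters in each arm") and takes 65 people tested per cluster as the average. It gives a between-community SD of 8.45% and a coefficient of variation of 0.42.

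**The concern.** After one year of SHQIP in the first round, two rounds are still on usual care, not one. According to the Randomisation section, the next eight clusters were drawn only towards the end of the second year of the project, so during the first intervention year the other 16 clusters formed a single pool awaiting allocation. Third-round clusters are therefore controls of the same standing as second-round clusters: randomised, concurrent and surveyed. Using only half of that pool sets aside data the trial collects anyway.

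What is at stake is precision. The article says the study is powered to detect a halving of prevalence. If the one-year comparison has only about 60% power for that effect, a real halving would be missed about four times in ten.

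**Working it through.** **Inputs.** From the Sample size section: p0 = 0.15, p1 = 0.075, m = 65 per cluster, k = 0.42, two-sided 5%, 80% power. As alternatives: k = 0.0845/0.15 = 0.563 from the stated SD, and m = 100 from the planned survey size. Clusters per round: 24/3 = 8.

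**The plan's own figure.** Hayes–Bennett, unmatched, clusters per arm:

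c = 1 + (1.960 + 0.842)² × [p0(1−p0)/m + p1(1−p1)/m + k²(p0² + p1²)] / (p0 − p1)²

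Variance of a cluster's observed prevalence:
- usual care: s0² = 0.1275/65 + 0.42² × 0.15² = 0.00196 + 0.00397 = 0.00593
- SHQIP: s1² = 0.069375/65 + 0.42² × 0.075² = 0.00107 + 0.00099 = 0.00206

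c = 1 + 7.849 × 0.00799/0.005625 = 12.15, so 13 per arm and 26 in total. The stated 14 in total is not reproduced. With k = 0.563 the result is 17.7 per arm (36 in total); with k = 0.42 and m = 100 it is 10.7 per arm (22 in total). A total of 14 at m = 65 would need k of about 0.21. Inverting the formula, 7 v 7 has 54% power and 8 v 8 has 60%.

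**One-year contrast, k = 0.42, m = 65.**
- 8 v 8: SE = √(0.00206/8 + 0.00593/8) = 0.0316. Ratio 0.075/0.0316 = 2.37; noncentral t on 14 df gives 60%.
- 8 v 16: SE = √(0.00206/8 + 0.00593/16) = 0.0251. Ratio 0.075/0.0251 = 2.99; noncentral t on 22 df gives 82%.

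**Range over the inputs the article gives.**

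| k | m | SE 8 v 8 (points) | SE 8 v 16 (points) | Power 8 v 8 | Power 8 v 16 |
|---|---|---|---|---|---|
| 0.42 | 65 | 3.16 | 2.51 | 60% | 82% |
| 0.42 | 100 | 2.94 | 2.32 | 66% | 87% |
| 0.563 | 65 | 3.87 | 3.04 | 44% | 65% |
| 0.563 | 100 | 3.69 | 2.89 | 47% | 70% |

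**Dependence on the test.** In beta-binomial simulations at k = 0.42 and m = 65, GEE with a small-sample correction went from 64% to 79%, and a pooled-variance t-test on cluster prevalences from 61% to 73%. The pooled test gains less because the larger arm also has the larger variance, which inflates the pooled estimate.

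**Two-year contrast.** By then the second round has had a year of SHQIP, and the third round is the only one on usual care. No control cluster is left out. Power stays at about 60% for 15% v 7.5%, and reaches roughly 80% (79%) only for a fall to 6%.

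**Supporting stepped-wedge model.** The model has 24 clusters, four surveys, period effects and separate effects for one year and for two or more years. Against 8 v 8 it cuts the variance of the one-year effect by about 60–81% and of the two-year effect by about 33–57%. The between-year correlation of a cluster's prevalence is assumed here to lie between 0 and 1; the article does not give it. If the cluster SD scales with prevalence, the ranges are 63–75% and 44–58%.

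**The case against.** The best defence is that each planned contrast compares randomised groups at the same time. Both are valid, keep the one-year and two-year effects apart, and need no model of secular trend. That stands: nothing here shows bias or an inflated false-positive rate. But it does not explain the exclusion of the third round at one year, because 8 v 16 has the same virtues.

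Four stronger readings are tempting, and the article does not support them.

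- *Both main analyses discard usual-care controls.* Only the one-year analysis does. The two-year analysis omits the second round, which is then on SHQIP with shorter exposure and belongs on neither side of a clean two-year contrast.
- *The choice of contrasts costs the trial its stated power.* The stated 80% is attached to 14 clusters in two equal arms, and each contrast has 16. No power was claimed for 24 clusters or for a stepped-wedge model. The shortfall arises because 14 does not follow from its inputs.
- *Each analysis uses a single survey and ignores baseline.* The article names groups and time points, not the data that enter the model. It plans mixed models or GEE, with adjustment if baseline covariates are imbalanced. Use of the baseline survey may be settled in a fuller plan that is not shown.
- *The 14 is a per-arm number misprinted as a total.* Per-arm results that round up to 14 do occur (13.15 with the matched formula; 13.4 unmatched at m = 50), but the article does not say so.

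It is also fair to object that 8 v 16 does not secure 80% in every case. At k = 0.563 it reaches 65–70%, and it does nothing for the two-year contrast.

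**Conclusion.** The point holds for the one-year analysis. As written, it omits eight equally valid concurrent controls. Including them cuts the standard error by about a fifth (2.51/3.16 = 0.79) and adds roughly 20 percentage points of power in every scenario the article's inputs allow: 60% to 82% at k = 0.42 and m = 65, and 44% to 65% at k = 0.563 and m = 65. These figures assume 15% v 7.5%, eight clusters per round, equal cluster sizes, and a test that allows for the arms' different variances. The loss is one of precision, not validity.

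The two-year contrast is sound in its choice of controls but has only about 60% power at k = 0.42 and m = 65. That shortfall, and the apparent adequacy of 8 v 8 in general, go back to the 14-cluster figure, which the section's own inputs do not reproduce.

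**What to change.** 1. Define the one-year main analysis as first-round clusters against second- and third-round clusters combined (8 v 16), using an analysis that does not assume equal variances across arms. Keep first v second round as a sensitivity analysis. Settle this before the one-year results are examined.
2. Keep first v third round at two years. Add, as a supporting analysis, a stepped-wedge model on all 24 clusters and all annual surveys, with period effects and separate effects for one year and for two or more years of SHQIP. State the assumed correlation structure. Reasonable statisticians could differ on making this model primary, because its gain rests on that structure.
3. Restate the power section. Correct or explain the 14, reconcile the SD of 8.45% with the coefficient of 0.42 and the 65 tested with the planned 100, and give power separately for the one-year and two-year contrasts.

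Items 1 and 3 change wording only, need no new data and bring in no new modelling assumption. Item 2 costs some analysis time.
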